**Methods/Design:**

The ongoing study of bricklayers and supervisors is a nonrandomised trial to compare the outcome of an intervention (job-specific WHS) group (n = 206) with that of a control (WHS) group (n = 206). The study includes a three-month follow-up. The primary outcome measure is the proportion of participants who have undertaken one or more of the preventive actions advised by their occupational physician in the three months after attending the WHS. A process evaluation will be carried out to determine context, reach, dose delivered, dose received, fidelity, and satisfaction. The present study is in accordance with the TREND Statement.

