### Recruitment of occupational physicians

Participating OPs are recruited between October and December 2011 from offices of the same OHS. These offices are geographically widespread over the Netherlands and were selected on the basis of i) the number of bricklayers and supervisors expected to be invited for a WHS in 2012 and, for the intervention group, ii) the possibility of setting up a job-specific WHS. To provide a safe testing situation, the office must have a covered accommodation of approximately 15 × 15 m and the ability to set a 7 m ladder up against the building.

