#### Sample size and assignment

The sample size is based on detecting a difference in activities or interventions undertaken by the worker in the six months after they have attended their WHS. No information on this is available from literature. From the registered activities and interventions in the Arbouw-database, we expect 10% of the workers in the control group to undertake an activity registered by the OP. We have decided that an absolute increase of 20% in interventions undertaken by the workers is a relevant difference. For an increase of 20% (from 10 to 30%) with alpha 0.05 (two-tailed) and a power of (1-beta) = 0.80, power calculation using the Nquery Advisor software results in 75 workers per group. However, we expect a small effect at the level of the OP (ICC = 0.01). Every OP will treat ~15 workers. This results in a design effect of 1.14 ((1+(N-1)*ICC) and an adjusted sample size of 86 per group, divided over at least 6 OPs [16]. With an expected loss to follow-up of 20% and an initial attendance of 50% at the OHS, we must invite 206 workers per group (103 bricklayers, 103 supervisors).

We do not expect major differences between the various offices of a single coordinating OHS. No restrictions or matching criteria were imposed.

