### Statistical analysis

The baseline data and the primary and secondary parameters will be presented using descriptive statistics. The following characteristics at baseline will be compared between the intervention and control groups: occupation, work experience in years in construction and in the current occupation, work hours per week and any possible worker compensations such as early retirement or partial disability. Furthermore, these characteristics will be compared overall and by study condition in those lost to follow-up and those retained. Moreover, the age and occupation of the study population at baseline and target population (all invited by the OHS) will be compared. Differences in continuous outcome measures will be tested with an independent samples T-test, differences in proportions will be tested with a Chi-Square test.

The effectiveness of the job-specific WHS on the primary and secondary outcome measures will be analysed on the individual level. First, data for the whole group will be analysed irrespective of the occupation of the worker. Second, subgroup analyses will be performed among the bricklayers and supervisors. For all analyses, a significance level of 0.05 will be applied. Workers with the same OP tend to be more homogeneous than workers with different OPs. Therefore, a two-level logistic regression model with workers at level 1 nested within OPs at level 2 will be used to analyse the binary data. The SPPS Advanced Statistics 19 software will be used to perform the logistic multilevel analysis by using a Generalised Linear Mixed Model (GLMM).

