### Limitations

The nonrandomised design of this study might be regarded as a limitation. We aim to contributing to evidence-based occupational health care, and in this context a randomised controlled trial is considered the gold standard to provide evidence for the effectiveness of an intervention. We considered randomisation at both the level of the individual worker and at the level of the OP, but we came across the practical limitations of a randomised trial. We felt that a nonrandomised design fit the best. In this way, we interfered as little as possible in the occupational health care routine for construction workers, which allowed us to evaluate the job-specific WHS in everyday practice.

We will perform subgroup analyses on the occupations, but we acknowledge the fact that our study cannot provide evidence of small differences. As we are dependent on the number of bricklayers and supervisors who are eligible for invitation by their OHS, the only possible solution would be to have more OHSs participating in the present study. In addition to the excessive extra costs, this solution would result in relatively few extra workers per OHS, as we already selected the largest offices of the OHS. Another obstacle is the economic recession, which results in a high percentage of dismissed workers in the construction industry.

The results of the present study will be available in 2013.

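### In a nonrandomised comparison of offices, the stated effect model names no baseline covariate, so the arm effect is open to confounding by worker characteristics the trial already records

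*Protocol article*

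**What the plan says.** The abstract of the Protocol article (Methods/Design) describes a study that "is a nonrandomised trial to compare the outcome of an intervention (job-specific WHS) group (n = 206) with that of a control (WHS) group (n = 206". Under Limitations, the authors write that "The nonrandomised design of this study might be regarded as a limitation" and defend the design on practical grounds, without naming an analytic remedy.

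Under Recruitment of occupational physicians, all offices were chosen on "the number of bricklayers and supervisors expected to be invited for a WHS in 2012". A second criterion applied to one arm only: "for the intervention group, ii) the possibility of setting up a job-specific WHS". This meant covered space of about 15 × 15 m and room for a 7 m ladder. Under Sample size and assignment, the authors expect no major differences between offices of the one occupational health service and add that "No restrictions or matching criteria were imposed".

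Under Study population and recruitment, workers invited at intervention offices receive a letter about the innovation. No such letter is described for control offices. Attendance is voluntary (Dutch context) and is planned at 50%. The primary outcome is counted among attenders.

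Under Statistical analysis, baseline data are handled thus: "The following characteristics at baseline will be compared between the intervention and control groups". The variables are occupation, work experience, work hours and worker compensations. Age is compared only between the study population and all those invited. For the effect, "a two-level logistic regression model with workers at level 1 nested within OPs at level 2 will be used to analyse the binary data". The main analysis pools the occupations, after which "subgroup analyses will be performed among the bricklayers and supervisors".

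**The concern.** Without randomisation or matching, the analysis is the main place left to control for differences between workers in the two arms. The plan states the model's levels, link and software but no adjustment set, and it gives no consequence if the baseline comparison shows a difference.

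There are two routes to arms that differ: how offices were chosen, and who attends once only one arm has been told of something new. If workers differ in age, experience or working hours, and these relate to acting on advice, the difference enters the estimated effect. The Discussion nevertheless expects to determine whether the job-specific approach results in more preventive actions, which is a causal statement.

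**Working it through.** **1. Can the OP random effect do the job?** Under Study design, each OP delivers one programme, and intervention OPs work at different offices from control OPs. OP is therefore nested within arm. The random effect accounts for correlation among workers of one OP. It carries no information that would remove a difference between arms.

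**2. Can the baseline tests do the job?** The plan's own per-group figure reproduces: design effect 1 + (15 − 1) × 0.01 = 1.14, and 75 × 1.14 = 85.5, rounded up to 86. With 86 per arm, a two-sided 0.05 chi-square test has about 75% power for a characteristic present in 40% v 60%, and about 50% for a 15-point imbalance centred on 50%, before clustering. A nonsignificant result does not show balance.

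**3. How large could the bias be?** The documents give neither the imbalance of any characteristic nor its association with the outcome, so the following are assumptions. For one binary factor with no true arm effect:

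bias = (prevalence in intervention − prevalence in control) × (outcome risk with the factor − risk without it)

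The risks are set so that the control arm has the stated overall rate and the factor has the stated odds ratio. Example, 10% control rate, 40% v 60%, odds ratio 3: risks are 6.0% without the factor and 16.0% with it. The control check is 0.6 × 0.060 + 0.4 × 0.160 = 0.10. Bias = 0.20 × 0.1005 = 0.020, or 2.0 points.

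The false-positive rate uses a normal approximation at two-sided 0.05 with effective size 206 × 0.5 × 0.8 / 1.14 = 72 per arm (the plan's invitations, attendance, retention and design effect).

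| Control rate | Prevalence, control v intervention | Odds ratio | Spurious difference | False-positive rate |
|---|---|---|---|---|
| 10% (plan) | 45% v 55% | 1.5 | +0.4 points | about 5% |
| 10% (plan) | 40% v 60% | 3 | +2.0 points | about 7% |
| 10% (plan) | 30% v 70% | 5 | +6.5 points | about 21% |
| 30% (assumed) | 45% v 55% | 1.5 | +0.9 points | about 5% |
| 30% (assumed) | 40% v 60% | 3 | +4.6 points | about 9% |
| 30% (assumed) | 30% v 70% | 5 | +14.1 points | about 43% |

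The sign is positive only because the factor was placed more often in the intervention arm. Reversing the imbalance would make the bias negative.

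**4. Is there room to adjust?** Expected events at the planned rates: 0.10 × 86 + 0.30 × 86 = 8.6 + 25.8 = 34.4, about 34. Arm plus five single-term covariates is six parameters, 34 / 6 = 5.7 events each. Arm plus one propensity score is two parameters, 34 / 2 = 17 events each.

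**The case against.** The strongest reply is that the article is silent on adjustment and does not exclude it. It lists no fixed effects at all, not even arm, and a condensed article may leave a covariate list to a fuller document. This stands as a limit on wording: a reader might infer that the plan forbids adjustment, and it does not. It does not dispose of the point, because the article gives the model, pools the occupations in the main analysis and assigns baseline data only to comparisons.

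A reader might also infer that the effect is confounded. The documents show no imbalance. The one-arm criterion concerns buildings, with no documented link to workers' behaviour, and both arms belong to one service and share the criterion on expected numbers. Invitations are planned at 103 bricklayers and 103 supervisors per arm, so occupation could drift only through attendance or loss. The absence of restrictions concerns assignment, since the same eligibility criteria apply to both arms.

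The larger biases need extreme inputs: an odds ratio of 5 with 30% v 70%, or a control rate above the plan's. At the planned rate the two milder cases give 0.4 and 2.0 points. That stands.

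Two cautions about the remedy also stand. Baseline work ability may not be comparable: the job-specific programme uses the first five questions of the work ability index, with an addition for supervisors, while care as usual scores work ability from an instrument the article does not name. And worker covariates cannot remove differences between offices or OPs, with about six OPs per arm.

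Whether the occupation subgroups should be compared through an interaction term is a separate question. The article does not say that two subgroup p-values will be set against each other.

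**Conclusion.** The point holds in this form: the arm effect is open to confounding by worker characteristics the trial already records, and the stated analysis contains no safeguard. It rests on the nonrandomised design, the unmatched offices with a one-arm criterion, the one-arm letter before voluntary attendance, and a model described only by its nesting.

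The size is not known. For a single binary factor at the planned 10% control rate, the assumed cases run from under 1 point to 6.5 points against a target of 20. The 14.1-point case needs a 30% control rate together with strong imbalance and association. Bias is small unless imbalance and association are both large, and its direction cannot be predicted. The documents do not support saying that the result will be biased, nor that the facility criterion proves the arms differ in prognosis.

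**What to change.** Make the primary analysis the same two-level logistic model, with arm plus a short covariate set fixed before outcome data are seen and kept whatever the baseline tests show: occupation, age, years in the current occupation, work hours per week and worker compensation. Add baseline work ability only if the same items are scored in the same way in both arms.

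With about 34 expected events, decide in advance between this list and a single propensity-score covariate built from it. Do not leave the choice until the data have been seen. Report the unadjusted model second.

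State as a remaining limitation that worker-level adjustment cannot remove office- or OP-level differences with about six OPs per arm.

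The cost is analysis wording, since these five variables are already recorded. The small downside is a few more parameters with few events, and the propensity-score form reduces it.

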### Study design

In the following description of the design of this study we follow the TREND Statement [14]. The primary objective of the study is to compare how attending a job-specific WHS versus the current WHS (care as usual, CAU) influences the preventive actions undertaken by bricklayers and supervisors (hereafter referred to as 'workers'). Our hypothesis is that the job-specific WHS helps bricklayers and supervisors undertake preventive actions.

Offices of one OHS participate in the study. At the offices of the OHS in the control group, the workers attend CAU. The OPs in the control group counsel their workers according to CAU. Workers in the intervention group attend the job-specific WHS, and the OPs in the intervention group counsel their workers according to the job-specific protocol. After inclusion and baseline measurements, measurements take place at two and three months after baseline. The medical ethics committee of the institution, the Academic Medical Center, approves the present study, and the board of the participating OHS advises positively about the local feasibility of the study.

Blinding of the OPs, physician's assistants, ergonomists or workers is not feasible for several reasons. The workers are familiar with CAU as they are invited regularly (every four or two years) for their WHS. Any modification to the standard procedure would be noticed. Moreover, every OP is trained to apply either the experimental intervention (job-specific WHS) or CAU. Therefore, all the OPs know which type of intervention they perform. To prevent contamination between the two groups, the OPs in the control group will neither be informed about nor receive training in the job-specific WHS. The OPs in the intervention group are requested not to disclose the new intervention during the length of the study to the OPs in the control group. Furthermore, the chance of contamination is small as the OPs in the intervention group work at different offices than the control group. The physician's assistants will be informed about the procedural changes in the job-specific WHS compared to CAU. The ergonomists will be trained to apply the experimental intervention only, as they do not contribute to the CAU.

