### Study population and recruitment

The research population includes all workers with the occupation bricklayer or supervisor who are invited by the OHS. Workers are eligible to participate when they are i) primarily working as a bricklayer or construction supervisor; ii) male; iii) able to read, speak and write Dutch sufficiently well and iv) not planning to leave their occupation in the three months after inclusion due to resignation or (early) retirement. Because both occupations consist primarily of men, we include only men.

The study population is recruited through the participating OHS. The workers, who are invited at the offices where the job-specific WHS is implemented, are informed by a letter about the innovation at their OHS. Then, concurrent procedures are performed for both the control and intervention groups: all workers are asked to confirm their attendance, and if necessary, another date or time is arranged. When a worker does not show up without cancelling, the OHS will try to follow-up by phone to make a new appointment if desired by the worker.

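### Treatment condition follows the office, but the primary model stops at the occupational physician; if an office holds several physicians and offices differ, the standard error for arm is too small

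*Protocol article*

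**What the plan says.** All of this is in the protocol article.

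- **Condition is set by office.** Study design: "At the offices of the OHS in the control group, the workers attend CAU", and "the OPs in the intervention group work at different offices than the control group". Study population and recruitment: the workers told of the new programme are those "invited at the offices where the job-specific WHS is implemented".
- **Intervention offices are selected differently.** Recruitment of occupational physicians lists an extra criterion: "for the intervention group, ii) the possibility of setting up a job-specific WHS".
- **The model has two levels.** Statistical analysis: "workers at level 1 nested within OPs at level 2", fitted as a logistic GLMM at a significance level of 0.05. No office term is mentioned.
- **Planning allows for the OP only.** Sample size and assignment uses an OP-level ICC of 0.01, about 15 workers per OP and a design effect of 1.14, giving 86 workers per group "divided over at least 6 OPs". On offices it says: "We do not expect major differences between the various offices of a single coordinating OHS".

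The article gives neither the number of offices nor the number of OPs per office.

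**The concern.** Because every office delivers one condition only, any difference between offices falls wholly between the arms. A random intercept for OP treats OPs as independent. If two or three of them work in one office and offices differ, their workers' outcomes are correlated beyond what the model allows, and the arm effect looks more precise than it is.

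The article itself gives reasons to doubt that offices are alike. They are spread over the country, the intervention offices had to pass a facility criterion that control offices did not, and the Process evaluation section plans to monitor organisational and economic context because it may influence delivery. The Limitations section says that the largest offices were selected, which makes several OPs per office plausible.

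A second, weaker matter is the small number of clusters. Arm varies only between clusters, so its test rests on about 12 OPs, or on fewer offices. A large-sample reference can then be too liberal even if the clustering level is right. What is at stake is the 5% level of the primary comparison.

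**Working it through.** **1. The plan's own figure.** Design effect = 1 + (15 − 1) × 0.01 = 1.14; 75 × 1.14 = 85.5, so 86 per group, as stated. 86 / 15 = 5.7, hence at least 6 OPs per group. With 206 invited and 50% attendance, 103 attend per group; 103 / 15 = 6.9, about 7 OPs. In all that is about 12 to 14 OPs, or 10 to 12 between-OP degrees of freedom.

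**2. Effect of leaving out the office.** Assumptions, not in the article: two OPs per office, 14 workers per OP (86 / 6 = 14.3), and a total within-OP ICC of 0.05, part of it at office level.

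- Design effect in the OP-only model: 1 + 13 × 0.05 = 1.65.
- True design effect: 1.65 + 14 × office ICC.
- Actual error of a nominal 5% test: 2 × (1 − Φ(1.96 × √(1.65 / true))).

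| Office ICC | OP ICC | True design effect | √ratio | Error |
|---|---|---|---|---|
| 0.01 | 0.04 | 1.79 | 0.960 | 6.0% |
| 0.025 | 0.025 | 2.00 | 0.908 | 7.5% |
| 0.05 | 0 | 2.35 | 0.838 | 10.0% |

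The last row is an extreme: it treats two OPs in one office as identical. With one OP per office the ratio is 1, because the OP effect then carries the office effect.

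**3. Simulation of the two-level logistic model.** 12 OPs with 14 workers each, no true effect, event rates of 10% and 20%, 1,500 runs per setting. The number of offices and all ICCs other than the OP value of 0.01 are assumed.

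| Offices per arm × OPs per office | OP ICC | Office ICC | Normal reference | t, 10 df |
|---|---|---|---|---|
| 6 × 1 | 0.01 | 0 | 4.3–6.3% | 1.9–2.9% |
| 6 × 1 | 0.05 | 0 | 7.5–7.9% | 3.7–4.1% |
| 6 × 1 | 0.10 | 0 | 9.9–10.5% | 6.3–6.5% |
| 3 × 2 | 0.01 | 0.01 | 7.9–8.3% | 3.8–4.8% |
| 3 × 2 | 0.01 | 0.05 | 13.1–13.7% | 8.8–9.6% |

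The normal-reference figures for 3 × 2 combine both problems, so they exceed what step 2 would give. At an office ICC of 0.05, t on 10 df does not cure the omitted office. A t-test on office means held between 3.8% and 5.8% in every setting run.

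**4. Power for 10% versus 30%.** Analysed per group: 206 × 0.5 × 0.8 = 82.4. The standard error is √(0.30 × design effect / 82.4), where 0.30 = 0.1 × 0.9 + 0.3 × 0.7. Power is from the noncentral t.

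- Six clusters per arm, ICC 0.01, 10 df: design effect 1 + (13.7 − 1) × 0.01 = 1.13; standard error 0.064; 0.20 / 0.064 = 3.12; critical value 2.228; power 80%.
- Three offices per arm, ICC 0.01, 4 df: design effect 1 + (27.5 − 1) × 0.01 = 1.26; standard error 0.068; 0.20 / 0.068 = 2.95; critical value 2.776; power 60%.

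**The case against.** The plan does not ignore clustering. It applies a design effect, models the OP and states its assumption about offices openly. Four objections carry weight.

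- OPs per office is not reported. With one OP per office there is no fault in the model. This stands, and it makes the point conditional.
- The reference distribution is not stated, and that detail commonly belongs in an analysis plan, which is not shown. A reader might infer that a normal reference is planned; the article does not say so. This stands, and the small-sample part is the weaker one.
- At the planned ICC of 0.01 with offices alike, the error is near nominal. A reader might infer that the 5% level fails as soon as the OP ICC exceeds 0.01. It does not: 0.01 enters only the sample size, the model estimates OP variance from the data, and a larger value mainly costs power unless a large-sample reference is used.
- Ten degrees of freedom is a floor at OP level, since the plan says at least six OPs per group. It is not a floor at office level, where there may be fewer.

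What these do not answer is that the condition is set one level above the top level of the model, and that only an expectation without supporting figures covers the gap.

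**Conclusion.** The mismatch between the unit that carries the condition and the top level of the model is in the text. Its harm is conditional. It needs more than one OP per office and a real difference between offices. Given an assumed two OPs per office and a total ICC of 0.05, the analytic error is about 6% to 10% in place of 5%, by the office's share of the variation. With one OP per office it is nil.

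The small number of clusters adds a separate risk, again only if a large-sample reference is used: about 7.5% to 10% at OP ICCs of 0.05 to 0.10.

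A reader might conclude that the primary test will understate uncertainty. The article does not support that without qualification, since it leaves open both the OPs per office and the reference, and no document gives an office ICC. The point is worth correcting before analysis because the 5% level otherwise rests on an untested expectation.

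**What to change.** - State the number of offices and of OPs in each arm.
- Where an office has more than one OP, make office the clustering unit: a random intercept for office with OP within it, or a t-test on office proportions.
- Test arm with between-cluster degrees of freedom and say which method is used (for example Satterthwaite).

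No new data are needed beyond recording each worker's office. The cost is a wider interval. With about six clusters per arm and an ICC of 0.01, power stays about 80%. With only three offices per arm it is about 60%, and the stated power of 80% should then be restated. That loss reflects uncertainty already in the design, which an OP-only model would not show.
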